### 10.3 Characterization of Properties

The app includes 1) an analysis of the individuals smoking history, 2) two questionnaires for lung-related symptom data and psychosocial wellbeing, 3) smoking diary to enhance self-reflection, and 5) virtual supportive channel providing evidence-based data on the benefits of smoking cessation.

The app aims to:

- Provide analytical data for the user's smoking behavior based on the background data provided by the user and smoking behavioral analysis done using the software
- Help out in making a personalized smoking cessation plan based on users smoking behavioral profile
- Provide behavioral support for smoking cessation
- Provide information on the health benefits of smoking cessation

- Provide long-term follow-up data on user's health status based on symptoms questionnaires and facial photos
- Provide behavioral support for remaining smoking-free after cessation
- Provide data for further development of the application to enhance its performance in smoking cessation and improve the user experience

## 11. CONCOMITANT INTERVENTIONS

### 11.1 Prohibited Interventions

- Use of another application for smoking cessation
- Participation in another lung cancer screening pilot or trial

### 11.2 Trial Subject Withdrawal/Discontinuation

Subject's participation in the study must be discontinued for any of the following reasons:

- Withdrawal of informed consent
- In the case of any clinical adverse event (AE), laboratory abnormality or illness leading to the conclusion by the investigator that participation into the trial is not the best interest of the subject
- Pregnancy
- Termination of the trial by the Sponsor
- Loss of ability to freely provide informed consent
- Inability to comply with protocol

All trial subjects should comply with the protocol specified follow-up procedures. The only exception to this requirement is a withdrawal of informed consent for all trial procedures or when a subject has lost the ability to consent freely. All data collected until the withdrawal of informed consent will be analyzed and included into trial data.

## 12. ADVERSE EVENT REPORTING

The objective of adverse event (AE) reporting is the documentation of all events occurring that may compromise the welfare and safety of trial participants. Adverse event reporting is to be distinguished from the collection of data for purposes of analyzing trial endpoints, which is achieved through the recording of specific data elements on case report forms and statistical analyses.

### 12.1 Definition of Adverse Event

An Adverse Event (AE) is any unfavorable and unintended sign, symptom, or disease temporally associated with the use of a medical treatment or procedure regardless of whether it is considered related to the medical treatment or procedures (attribution of unrelated, possible, probable, or definite).

### 12.2 Definition of Serious Adverse Event

A Serious Adverse Event (SAE) is any adverse event that results in any of the following:

- Death
- In-patient hospitalization (for reasons other than observations) or prolongation of an existing hospitalization

- A persistent or significant disability or incapacity
- Congenital anomaly/birth defects

### 12.3 Characterizing Adverse Events by Attribution and Severity

Once identified, the site PI should characterize the AE by attribution (whether it is related to a trial-related procedure) and grade of severity. The following guidelines apply:

The attribution of an AE or SAE characterizes its causal relationship to the trial-related procedure as follows:

- Unrelated – clearly NOT related to procedure
- Possible – may be related to procedure
- Probably – likely related to procedure

Grade denotes the severity of the AE and is graded according to the current version of the Common Terminology Criteria for Adverse Events (CTCAE v6.0), or the following categories (if the term does NOT appear in the CTCAE v6.0):

- 1 – Mild
- 2 – Moderate
- 3 – Severe
- 4 – Life-threatening or disabling
- 5 – Fatal

#### 12.3.1 Direct and Indirect AEs in Screening Imaging Trials

- Complications associated with primary interventions are termed direct AEs
- Screening tests promote downstream, diagnostic interventions; complications associated with these diagnostic interventions are termed indirect AEs
- In this protocol, **only direct adverse events associated with the primary trial interventions will be reported as adverse events**

### 10.5 AE/SAE Recording and Reporting Period

Details of all AEs will be recorded from the date of consent until the AEs have resolved or no change of the AE status is observed during the last study visit. If the subject is withdrawn from the study, the subject must be followed up for open AEs until the AE has resolved, or no change in subject status is observed over the follow-up period.

## 13. Device Safety

### 13.1 Safety Plan

Several measures will be taken to ensure the safety of participants in this study. Participants will undergo safety monitoring during the study, including assessment of the nature, frequency, and severity of adverse device effects. In addition, guidelines for managing adverse device effects, including criteria for the application discontinuation, are provided below.

#### 13.1.1 Risks Associated with the smoking cessation application

The smoking cessation application is fully GDPR compliant.

Potential risks have been assessed according to the sponsor's assessment processes and categorized by severity and probability of occurrence.

Risks related to confidentiality, integrity, and/or availability of the personal data processed by the sponsor cannot be completely eliminated. If you suspect that your personal data has been compromised, please contact the study sponsor.

### 13.2 Management of Participants Who Experience Adverse Device Events

#### 13.2.1 Safety Parameters and Definitions

Safety assessments will consist of monitoring and recording adverse device effects, including serious adverse device effects.

Certain types of effects require immediate reporting to the Sponsor.

##### 13.2.1.1 Adverse Device Effect

An adverse device effect is any adverse event that is related to the use of an investigational health device (smoking cessation application). This includes adverse events resulting from insufficient or inadequate instructions for use, deployment, implantation, installation, or operation, or any malfunction of the investigational health device. This definition includes any event resulting from use error, or from intentional misuse of the investigational health device.

##### 13.2.1.2 Serious Adverse Device Effects

A serious adverse device effect is an adverse device effect that has resulted in any of the consequences characteristic of a serious adverse event. Serious adverse device effects are either anticipated or unanticipated.

An anticipated serious adverse device effect is a serious adverse device effect, which by its nature, incidence, severity, or outcome has been identified. An unanticipated serious adverse device effect is a serious adverse device effect, which by its nature, incidence, severity, or outcome, has not been identified in the Risk Assessment Report. This includes unanticipated procedure-related serious adverse events; that is, serious adverse events occurring during the study procedure that are unrelated to any malfunction or misuse of the investigational medical device.

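### Protocol 13.2.1.2 lets procedure-related serious events with no link to the app be classed as serious adverse device effects, contradicting 13.2.1.1 and its own opening sentence

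*Protocol*

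**What the plan says.** Protocol 13.2.1.1 sets the test for a device effect: "An adverse device effect is any adverse event that is related to the use of an investigational health device (smoking cessation application". Protocol 13.2.1.2 builds on it: "A serious adverse device effect is an adverse device effect that has resulted in any of the consequences characteristic of a serious adverse event". It divides these into anticipated and unanticipated effects and then widens the second class: "This includes unanticipated procedure-related serious adverse events", which it explains as "serious adverse events occurring during the study procedure that are unrelated to any malfunction or misuse of the investigational medical device".

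Attribution is handled in section 12. Under 12.3 the site is to "characterize the AE by attribution (whether it is related to a trial-related procedure) and grade of severity", and the scale "characterizes its causal relationship to the trial-related procedure as follows": unrelated, possible, and a top level worded "Probably – likely related to procedure". The adverse event definition in 12.1 names four levels: "attribution of unrelated, possible, probable, or definite".

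Section 13.1 says that safety monitoring will include how often device effects occur, and their nature and severity. Section 13.2.1.3 states that no serious ones are anticipated.

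**The concern.** The device here is a phone app. The study procedures in the ordinary sense are LDCT and blood sampling, and both arms undergo them. A clause that brings in procedure-related serious events without asking for a link to the app therefore mixes two sources of harm under the app's name. The wording would suit a device whose use is itself the procedure, such as an implant; it does not suit this one.

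What is at stake is the reported safety of the app. Because no serious device effect is anticipated, a single misplaced procedure event could be the entire serious signal attributed to the app. It would also carry the label unanticipated, in a part of the protocol where 13.2.1 says that some effects need immediate reporting to the sponsor.

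**Working it through.** The protocol states no figure on this point, so the check is a comparison of definitions.

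1. **The test.** 13.2.1.1 requires a relation to use of the app. Malfunction, use error and intentional misuse all fall inside it.
2. **The subset.** The first sentence of 13.2.1.2 makes a serious device effect a device effect with a serious consequence, so the relation to the app carries over.
3. **The added class.** The later sentence admits events unrelated to malfunction or misuse. Two kinds fit that description: events from normal use of the app, and events with no connection to the app. The first kind is already covered by step 1, so the sentence adds nothing there. The only events it can add are of the second kind, and steps 1 and 2 exclude those.
4. **Device and procedure are distinct elsewhere.** The follow-up rule in 13.2.2.1 names the device and study-related procedures as alternative causes. 13.2.1.2 merges what 13.2.2.1 separates.
5. **Who can be affected.** Under 7.3 all subjects have LDCT within six weeks of randomization. Under 7.2 and 10.1 controls are offered the app only after six months. A control with a serious event at the first LDCT therefore meets the literal wording of 13.2.1.2 without having had the app.
6. **Whether the attribution scale corrects this.** The graded scale in 12.3 rates relation to one undivided procedure. 12.3.1 likewise speaks of the primary trial interventions together. Neither yields a graded rating for the app alone.
7. **Levels.** 12.1 has four, 12.3 has three; definite is missing from 12.3. An event that would have been definite is recorded at the top level available and still counts as related.

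**Illustration of scale (assumed rates, not in the protocol).** Let q be the proportion of subjects with a serious procedure-related event; for controls, before they have the app. With the maximum of 200 subjects randomized 1:1, there are 200/2 = 100 controls. The expected number of controls meeting the wording is 100 × q, and the chance of at least one is 1 − (1 − q)^100.

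| Assumed q | Expected in 100 controls | Chance of at least one control | Expected in all 200 |
|---|---|---|---|
| 0.1% | 0.1 | 1 − 0.999^100 = 10% | 0.2 |
| 0.5% | 0.5 | 1 − 0.995^100 = 39% | 1.0 |
| 1% | 1.0 | 1 − 0.99^100 = 63% | 2.0 |

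Under a definition confined to app-related events, the number in controls before app access is 0 at every q. The answer depends wholly on q.

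**The case against.** The best reply is that 13.2.1.2 should be read as a whole. Its opening sentence confines serious device effects to device effects, so the later sentence could be taken to cover only events already related to the app. On that reading no control without the app could qualify. In addition, unrelated to malfunction or misuse is not the same as unrelated to the app, and the term study procedure is not defined there.

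This is a possible reading, but it makes the sentence redundant (step 3), and the text expressly names procedure-related events. An investigator applying it case by case could reasonably follow the literal wording.

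Other parts of the reply stand and limit the point:

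- A reader might infer that app-related events cannot be isolated at all. The documents do not support that. 13.2.1 has device effects recorded as their own class, 13.2.1.1 makes relation to the app the defining test, and 13.2.2.1 and 13.2.3 call for a judgement of relation to the device, though without a graded scale. The adverse event form is not shown and may already hold such a field.
- A reader might infer that the missing definite level distorts the number of related events. It does not; it loses only information on certainty.
- No device-harm rate or between-arm safety comparison is listed as an outcome. That is correct, but 13.1 still commits the trial to assessing the frequency of device effects, so the classification feeds something planned.
- Controls are certain to be without the app only before month 6.

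**Conclusion.** Wrong as written, and minor. 13.2.1.2 contradicts 13.2.1.1 and its own first sentence, and its literal wording allows a serious LDCT or blood-sampling event to be classed as a serious app effect, in either arm. The mismatch of attribution levels between 12.1 and 12.3 is an editorial inconsistency.

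A reader might go further and infer that the count of app harms is wrong. The documents support only that it can be wrong: misclassification is permitted, not shown. Its size cannot be stated, because the protocol gives no rate of serious procedure-related events; the rates in the table are assumptions. An upper confidence limit for zero events across all scans would not help either, since it says nothing about how likely a misclassification is. Few or no such events are expected. An event must meet the seriousness criteria of 12.2, and 12.3.1 keeps complications of downstream diagnostic work-up out of adverse event reporting.

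The conclusion assumes that study procedure in 13.2.1.2 includes LDCT and blood sampling, which the protocol does not say in that place but which 13.2.2.1 makes the natural reading.

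**What to change.** - In 13.2.1.2, delete the sentence that adds procedure-related serious events, or move those events to a separate class of procedure-related serious adverse events. Serious events remain reportable under 12.4, so no safety information need be lost. It would help to state that LDCT and blood sampling both count as primary interventions for 12.3.1, if that is intended.
- In 12.3, rate relatedness to the app separately from relatedness to LDCT or blood sampling.
- Use one set of attribution levels in 12.1 and 12.3.

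The cost is one sentence removed or moved, one scale aligned, and one added field on the adverse event form if it does not already exist. Design, sample size and outcomes are unaffected.

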#### *13.2.1.3 Anticipated Adverse Device Effects and Anticipated Serious Adverse Device Effects*

Per the investigational device's labelling, no serious adverse device effects are anticipated.

#### *13.2.1.4 Device Deficiency*

A device deficiency is defined as any inadequacy in the identity, quality, durability, reliability, usability, safety, or performance of an investigational device, including malfunction, use errors, or inadequacy of manufacturer-supplied information.

All device deficiencies must be recorded on the eCRF. An assessment must be made as to whether the device deficiency could have led to a serious adverse device effect if:

- Appropriate action had not been taken,
- Intervention had not occurred, or,
- Circumstances had been less fortunate.

#### *13.2.1.5 Serious Health Threat*

A serious health threat is defined as a signal from any adverse device effect or device deficiency that indicates an imminent risk of death or a serious deterioration in the health in participants, users or other persons, and that requires prompt remedial action for other participants, users or other persons. This would include events that are of significant and unexpected nature such that they become alarming as a potential serious health hazard or possibility of multiple deaths occurring at short intervals.

### *13.2.2 Follow-up of Participants after Adverse Device Effects*

#### *13.2.2.1 Investigator Follow-up*

The investigator should follow each adverse device effect until the event has resolved to baseline or better, the event is assessed as stable by the investigator, the participant is lost to follow-up, or the participant withdraws consent. Every effort should be made to follow all serious adverse device effects considered to be related to the device or study-related procedures until a final outcome can be reported.

During the event reporting period, resolution of adverse device effects (with dates) should be documented on the CRF and in the participant's medical record to facilitate source data verification.

#### *13.2.2.2 Sponsor Follow-up*

For serious adverse device effects and device deficiencies that could have led to a serious adverse device effect, the Sponsor or a designee may follow up by telephone, fax, email, and/or a monitoring visit to obtain additional case details and outcome information (e.g., from hospital discharge summaries, consultant reports, autopsy reports) in order to perform an independent medical assessment of the reported case.

### *13.2.3 Adverse Device Effects That Occur after the Adverse Device Effect Reporting Period*

The Sponsor should be notified if the investigator becomes aware of any serious adverse device effect that occurs after the end of the adverse device effect reporting period (withdrawal from the study), and if the event is believed to be related to the device. These events should be reported through use of the CRF.

## **14. DATA HANDLING AND RECORD KEEPING**

### **14.1 Data Collection**

All relevant data related to safety and efficacy including laboratory values and clinical parameters should be recorded in the medical records and be captured in the CRF. The site is responsible for completing

the CRF forms in a timely manner. All data on the eCRFs must be verifiable in the source data/hospital or patient records, unless eCRF data are declared as source data.

#### 14.2 Device Data

Data will be collected within a cloud-based platform(s), for processing, analysis and storage, managed by the sponsor. Only identified and trained users access this system. Device data may be analyzed on an ongoing basis for the purpose of device changes.

#### 14.3 Archiving

It is the responsibility of the Principal Investigator to ensure all essential trial documentation and source records (e.g. signed Patient Information and Consent Documents, Investigator Site Files, patients' hospital notes, copies of CRFs etc.) are stored in secure archives for 15 years after the end of the trial. However, these documents should be retained for a longer period if required by applicable legal requirements. The Sponsor's approval is required prior to transfer or destruction of the documents.

### 15. QUALITY MANAGEMENT

This trial is to be conducted according to the ICH harmonized tripartite guideline for good clinical practice E6(R2) and the European Union directive 2001/20/EC to ensure that the rights, safety and well-being of trial subjects are protected, consistent with the principles that have their origin in the Declaration of Helsinki, and that the clinical trial data are credible.

For the trial to start, all required documentation must be approved by the relevant ethical committees and competent authorities, in accordance with local legal requirements. The Sponsor must ensure that all ethical and legal requirements have been met before the first subject is enrolled in the trial.

This protocol is to be followed exactly. To alter the protocol, amendments must be written, receive approval from the appropriate personnel, and receive ethical committee/competent authority approval prior to implementation (if appropriate).

Administrative changes (not affecting the subject benefit/risk ratio) may be made without the need for a formal amendment. All amendments will be distributed to all protocol recipients, with appropriate instructions.

#### 15.1 Site Set-up and Initiation

All participating Investigators will be asked to sign the necessary agreements and supply a current CV to the Sponsor or representative of the Sponsor. All members of the site research team that will perform study specific activities will also be required to sign the "Site Staff Signature and Task Delegation Log". Prior to commencing recruitment, all sites will undergo a process of initiation. Key members of the site research team will be required to be trained by the Sponsor, or a representative of the Sponsor, covering aspects of the trial design, protocol procedures, Adverse Event reporting, collection and reporting of data and record keeping. The investigators are responsible for ensuring that appropriate training relevant to the study is given to the medical, nursing and other personnel involved in the study. The investigators will also ensure that any information relevant to the conduct of the study is forwarded to the sub-investigators and other relevant study center personnel. Sites will be provided with an Investigator Site File containing essential documentation, instructions, and other documentation required for the conduct of the trial. The Sponsor or representative of the Sponsor must be informed immediately of any change in the site research team.

## 15.2 On-Site Monitoring

A separate Site Monitoring and Management Plan is available where full details of the monitoring activities are described. The trial is conducted according to the GCP and quality standards. Monitors must ensure that the required documentation and trial site training has been done before the site can start enrolling subjects. During the treatment phase, the site(s) will be monitored to ensure protocol adherence and to verify the source data. Any issues in compliance will be reported to the Sponsor.

By participating into this trial, the Investigator(s) and the site(s) conducting this trial will permit trial-related monitoring, audits, Institutional Review Board or equivalent review, and regulatory inspection(s) and provide direct access to source data/documents. A reasonable time must be given for the site(s) to prepare for such activities.

## 15.3 Audit and Inspection

The Investigator will permit trial-related monitoring, audits, ethical review, and regulatory inspection(s) at their site, providing direct access to source data/documents. Sites are also requested to notify the Sponsor of any relevant regulatory authority inspections.

## 15.4 Notification of Serious Breaches

The sites and the Sponsor of the trial will report any serious breaches or protocol/ICHGCP deviations in accordance with the local laws and current regulations. A “serious breach” is a breach which is likely to effect to a significant degree:

- The safety and rights of a subject.
- The reliability and robustness of the data generated in the clinical trial.

Where the Sponsor is investigating whether or not a serious breach has occurred, sites are also requested to cooperate with the Sponsor in providing sufficient information to report the breach to the relevant regulatory authorities/ethics committees where required and in undertaking any corrective and/or preventive action.

